#### Statistical analysis

The primary purpose of this trial is to assess the “optimal minimal dose” -- the minimal dose offering the most benefit while having adequate adherence (i.e., at least 80% of participants attending at least 75% of the treatment sessions) and no serious adverse events possibly attributable to massage. We will analyze the benefit of each “dose” for 3 overlapping subsets of our total number of study participants. Our primary analysis will be intention to treat and thus will include data for all participants, regardless of their treatment adherence. We will also conduct a pre-specified subgroup analysis for participants attending at least 75% of their treatment sessions. We will then conduct two per protocol analyses using the total hours of massage participants actually received over the four weeks, regardless of specific group. The first per protocol analysis will include all randomized treatment groups. This analysis may include the observations from the waitlist control group after they receive treatment to increase power as long as their outcomes after receiving treatment are shown to be similar to group 2 who were randomized to receive 60 min of massage once per week. The second per protocol analysis will also include the natural history control arm. We will first compare the natural history control arm and the waitlist control group at 5 weeks to make sure that this non-randomized control arm has comparable outcomes compared to the randomized waitlist group. We will make the comparisons adjusting for baseline characteristics. If the waitlist control group and the natural history control group are comparable we will conduct per protocol analyses including the natural history control group. Both per protocol analyses are exploratory analyses.

##### Primary treatment period: primary study outcomes at 5 weeks

The primary analyses will look at binary outcomes: 1) improvement of at least 5 points from baseline Neck Disability Index score and 2) improvement of at least 30% from baseline on the pain intensity score. We will use the following logistic regression model,

(1.1)$$\;\begin{array}{cc} \text{logit}\left(Y_{i}\right) & =\beta_{0}+\beta_{1}Group2_{i}+\beta_{2}Group3_{i}\\ & \;+\beta_{3}Group4_{i}+\beta_{4}Group5_{i}\\ & \;+\beta_{5}Group6_{i}+\alpha {Ζ}_{i} \end{array}$$

where *GroupA*_*i*_ is an indicator variable of 1 if participant i was randomized to group A or 0 otherwise (A=2, 3, 4, 5, or 6) and Z_*i*_ is a vector of potential confounders including baseline outcome score. We will use the Fisher’s protected least significant approach to assess if there are any differences among the 6 Groups and then, if there is a significant difference, to assess if any pairwise differences are significant. It is also of interest to run a parametric model to evaluate a trend over the weekly dose while taking into account the number of visits. In standard dosing analyses, at the lower doses, the proportion of patients improves with increasing dose, but as the dose increases to some higher level, further improvement is attenuated and approaches a threshold (see Figure
2).

**Figure 2 F2:**
[figure not shown]
Standard dose response curves with a threshold effect.

In our study, it is not readily obvious what would be defined as a high dose or a low dose. Is a high dose determined simply by total dose or is it influenced by the number of visits given in a week? Our sample size calculations assume that dosing is a combination of both total dose and the number of visits. Because our design is a partial factorial design we are not able to run the full model including an interaction between cumulative dose and an indicator variable for each number of doses given. We can, however, evaluate the following model,

(1.2)$$\;\begin{array}{cc} \text{logit}\left(Y_{i}\right) & =\beta_{0}+\beta_{1}TotalDose_{i}+\beta_{2}NumVisits1_{i}\\ & \;+\beta_{3}NumVisits2_{i}+\beta_{4}NumVisits3_{i}+\alpha Z_{i} \end{array}$$

where *TotalDose*_*i*_ is the total number of minutes per week a participate is randomized to (e.g. Group 2 (60 min/week) is 60 min and Group 3 (30 min/2-week) is also 60 min), *NumVisitsB*_*i*_ is an indicator variable of 1 if participant *i* was randomized to a group with B visits per week or 0 otherwise (B=1, 2, or 3) and Z_*i*_ is a vector of potential confounders, including baseline outcome score.

Applying this model, we are able to assess, given a specific number of massages per week, if there is any significant linear trend in total dose. Because our dosing schedule includes multiple groups receiving either 2 or 3 visits per week (Groups 3 and 4 receive 2 doses per week and Groups 4 and 5 receive 3 doses per week), we will only be able to assess a linear trend of improvement in individuals in those pairs of groups. This would allow us to assess whether the number of doses, adjusted for total dose, is a significant predictor of outcome (*H*_*o*_: *β*_1_ = 0). Figure
3 displays an example of possible results from Model 1.2.

**Figure 3 F3:**
[figure not shown]
Plot of potential results from model 1.2 assessing the effect of total dose and number of weekly visits on proportion of improvement from baseline response.

Model 1.1, the main effects model including all indicator variables, allows us to determine which groups differ from each other in terms of overall improvement. However, we have relatively low power to show a significant difference between groups 4, 5, and 6. Therefore, a failure to find a significant difference between groups 4, 5, and 6 could reflect a lack of power or a true absence of additional benefit (i.e., a thresholding effect; see Figure
2). Therefore we will also run the following model, not adjusting for number of visits, to evaluate a general trend of total dose,

(1.3)$$\;\log it\left(Y_{i}\right)=\beta_{0}+\beta_{1}TotalDose_{i}+\beta_{2}TotalDose_{i}^{2}+\alpha Z_{i}$$

If the quadratic term is not statistically significant then this would indicate no thresholding effect. We will also run more flexible models, such as splines, to assess an overall thresholding effect for benefit
[35].

We will apply the same models specified above for our secondary analyses, but will use linear regression models for the continuous outcomes.

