### Statistical issues

#### Sample size and the detectable difference

Our sample was chosen to ensure adequate power to detect a significant difference between at least two of the 5 groups receiving a massage treatment in the first 4 weeks of the trial (and not just adequate power to find a difference between one or more of the treatment groups and the waitlist control group). This reflects the primary goal of the trial: to compare the effects of different doses of massage on neck-related disability, and not just to determine if massage is better than no-additional treatment (as in the waitlist control). Our primary outcome is the binary measure of clinically relevant improvement of at least 5 points on the Neck Disability Index (NDI) at 5 weeks compared to baseline NDI score
[31]. Based on findings in our pilot study, we assumed that 7% of the waitlist control group and 35% of Group 2 (60-min weekly treatment) would improve. We lack pilot data to estimate improvement rates in the other groups. Therefore, to permit sample size estimation, we will assume that treatment benefits will increase with the number of treatments given per week (for a fixed weekly dose) and with the number of minutes of massage per week. We assume a two–fold improvement from the lowest to the highest weekly dose (i.e., 60 to 180 min), based on the expectations of our consultant massage therapists. Table
4 summarizes our assumptions for both the NDI and neck bothersomeness score.

**Table 4 T4:** Assumptions for sample size calculations

**Group**	**Amount of massage (weekly dose)**	**Proportion with clinically relevant improvement on NDI (at least 5 point improvement)**	**Proportion with clinically relevant improvement on Bothersomeness score (≥ 30% improvement)**
1	Waitlist	0.07	0.10
2	60 min 1×/week (60 min)	0.35	0.48
3	30 min 2×/week (60 min)	0.40	0.55
4	60 min 2×/week (120 min)	0.55	0.65
5	30 min 3×/week (90 min)	0.60	0.70
6	60 min 3×/week (180 min)	0.70	0.80

To protect against multiple comparisons, we will use Fisher’s protected least significant difference approach. Although this approach has been shown to inadequately protect against the type I error rate for studies with more than 3 groups,

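### The threshold in weekly minutes is read from Model 1.3, which leaves out number of visits, although the plan assumes that visits matter and the design ties the two together

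*Protocol article*

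**What the plan says.** All references are to the protocol article.

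- **Sample size and the detectable difference.** The planning premise is that "we will assume that treatment benefits will increase with the number of treatments given per week (for a fixed weekly dose"), and also with weekly minutes. Table 4 follows it. Group 3 (60 min in 2 visits) is set above Group 2 (60 min in 1 visit), and Group 5 (90 min in 3 visits) above Group 4 (120 min in 2 visits).
- **Primary treatment period: primary study outcomes at 5 weeks.** The section asks for a parametric trend over weekly dose that allows for visit frequency. It raises the question of whether dose means minutes or visits, and notes: "Our sample size calculations assume that dosing is a combination of both total dose and the number of visits." Model 1.2 then has total weekly minutes as a linear term plus indicators for number of visits.
- **Same section, after Figure 3.** Model 1.1 is said to have low power among Groups 4, 5 and 6, so that no difference there could mean either low power or a true plateau. For this reason "we will also run the following model, not adjusting for number of visits, to evaluate a general trend of total dose". This is Model 1.3, with minutes, minutes squared and baseline covariates. Its reading is fixed: "If the quadratic term is not statistically significant then this would indicate no thresholding effect." The text adds: "We will also run more flexible models, such as splines, to assess an overall thresholding effect for benefit." It does not say whether the splines contain a visit term, or whether the waitlist enters Model 1.3.

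**The concern.** The threshold question goes to a model that contradicts the plan's own premise about dose. In this design 90 min occurs only with 3 visits and 120 min only with 2. A curve that rises in minutes alone must therefore place Group 4 above Group 5, whatever those two groups show, and it must give Groups 2 and 3 the same fitted value. Whatever visits contribute is partly shown as an effect of minutes.

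Model 1.2 does not fill the gap. It adjusts for visits, but a linear dose term cannot show levelling off. Where Model 1.1 is inconclusive among Groups 4–6, the reader is sent to a curve that is misspecified in just that region. The Background treats session length and frequency as separate components of dose, so a statement about where minutes stop helping should not absorb the effect of frequency.

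**Working it through.** **Inputs.** From Table 4, for Groups 2–6 in order: minutes 60, 60, 120, 90, 180; visits 1, 2, 2, 3, 3; NDI rates 0.35, 0.40, 0.55, 0.60, 0.70; symptom rates 0.48, 0.55, 0.65, 0.70, 0.80. (Table 4 heads the symptom column as bothersomeness; the text applies it to pain intensity.) The waitlist rates are 0.07 and 0.10. Evaluable n is 34 per group and alpha is 0.05, taken as two-sided. Entering the waitlist as 0 min and 0 visits is my assumption.

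**The plan's own figures.** The plan states 80% power for Group 6 against Group 2. For the NDI (0.70 v 0.35) a logistic Wald test gives 81.9% and the normal approximation 84.0%. For symptoms (0.80 v 0.48) these are 80.4% and 79.9%. 34/(1 − 0.10) = 37.8, hence 38. The inputs are thus read as the plan reads them. The plan gives no figure for Model 1.3.

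**Step 1: correlation of minutes and visits, Groups 2–6.** The means are 102 and 2.2. The sum of cross-products is 50.4 + 8.4 − 3.6 − 9.6 + 62.4 = 108. The sums of squares are 10,080 and 2.8. r = 108/√(10,080 × 2.8) = 108/168 = 0.64. With the waitlist it is 0.82.

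**Step 2: Model 1.3 fitted to the exact Table 4 rates** (binomial, logit link, weight 34 per group, d = minutes/60). For the NDI in Groups 2–6, logit = −1.898 + 1.728d − 0.276d². Group 4 (d = 2) has logit about 0.45, a rate of 0.61. Group 5 (d = 1.5) has logit about 0.07, a rate of 0.52.

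**Step 3: the same with a linear visit term.** For the NDI, logit = −1.926 + 1.048d − 0.161d² + 0.356 × visits. Group 4 becomes 0.560 and Group 5 becomes 0.587.

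| Group 4 / Group 5 | Table 4 | Model 1.3 | Model 1.3 + visits |
|---|---|---|---|
| NDI, Groups 2–6 | 0.55 / 0.60 | 0.611 / 0.518 | 0.560 / 0.587 |
| NDI, with waitlist | 0.55 / 0.60 | 0.633 / 0.530 | 0.580 / 0.599 |
| Symptom, Groups 2–6 | 0.65 / 0.70 | 0.704 / 0.628 | 0.656 / 0.692 |
| Symptom, with waitlist | 0.65 / 0.70 | 0.743 / 0.653 | 0.698 / 0.715 |

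**Step 4: simulation under Table 4, n = 34 per group.** In Groups 2–6, Model 1.3 ranks Group 4 above Group 5 in about 99.8% of trials (NDI) and 99.4% (symptom). With the waitlist it is essentially 100%. The raw proportions rank Group 4 higher in only about 29%, so the reversal comes from the model and not from noise.

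**Step 5: how much visit effect is credited to minutes.** With a linear dose term (NDI, Groups 2–6), the log-odds per 60 min is 0.645 (odds ratio 1.91) without visits and 0.397 (1.49) with visit indicators, as in Model 1.2. 1 − 0.397/0.645 = 0.38, so about 38% of the unadjusted slope is visit effect.

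**Step 6: splines.** Without visits, a natural cubic spline with 2 df also reverses the two groups (NDI 0.611/0.518 in Groups 2–6). With 3 df and the waitlist it still does (0.591/0.529). With 3 df and no waitlist it is saturated in the four dose levels. It then returns 0.55/0.60, but as a dip in the minutes curve.

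**Step 7: price of the visit term (NDI, power of the quadratic test).** In Groups 2–6 the expected z moves from −0.76 to −0.43. At −0.43, power is Φ(0.43 − 1.96) + Φ(−0.43 − 1.96) = 0.063 + 0.008, about 7%. With the waitlist, z moves from −2.19 to −1.39, and simulated power falls from about 61% to 27%.

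**The case against.** The strongest reply is that the plan already deals with this. It raises the entanglement itself and supplies Model 1.2, and it labels Model 1.3 openly as unadjusted and supplementary. Comparisons between groups belong to Model 1.1. That stands, and it limits the point. A reader might infer that the optimal dose, or the ranking of Groups 4 and 5, would be taken from Model 1.3. Nothing in the document says so.

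A reader might also infer a high false-positive rate for minutes. If only visits mattered (illustrative rates 0.35, 0.50, 0.65 for 1, 2, 3 visits), a minutes-only linear trend would be significant in about 47% of trials and a free four-level dose curve in about 61%. The plan names neither test. Model 1.2, which it does name, rejects for minutes in about 5%, and the quadratic term of Model 1.3 in about 7%. Nor does every spline reverse the groups, and the text does not say that the splines omit visits.

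The benchmark is also soft. Table 4 is a planning assumption made without pilot data beyond Group 2 and the waitlist. With 34 per group, a five-point gap is not ranked reliably by any method: raw proportions put Group 5 strictly ahead in about 62% of trials, the visit-adjusted quadratic in about 62% (NDI), and Model 1.2 in about 69%. Lastly, the adjusted model has little power for curvature.

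What the reply leaves untouched is that Model 1.2 cannot show levelling off, and that the plan fixes a threshold conclusion on a model at odds with its own premise. Labelling the omission does not make that conclusion valid.

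**Conclusion.** The point holds for the supplementary dose-trend and threshold conclusion. Under the plan's own rates, Model 1.3 misorders Groups 4 and 5 for both outcomes, with or without the waitlist. On the NDI it overstates Group 4 by about 6 points and understates Group 5 by about 8 (Groups 2–6). The primary comparison (Model 1.1) and the visit-adjusted linear trend (Model 1.2) are not affected.

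The size rests on the Table 4 rates and 34 per group. That a rising minutes-only curve must place 120 min above 90 min does not depend on the rates. For the splines the point is conditional on their omitting visits, which their position directly after Model 1.3 suggests but the text does not state.

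**What to change.** - Add number of visits per week as a linear term to Model 1.3 and to any spline. In Groups 2–6 the extended Model 1.3 has four parameters for five groups and is estimable.
- State whether the waitlist enters these models, since the quadratic test depends strongly on it.
- Base any statement about a trend or threshold in minutes on the visit-adjusted fit, read together with Model 1.2.
- Keep minutes-only curves as description, with each dose level labelled by its number of visits.
- Remove the rule that a non-significant quadratic term indicates no threshold. At the power shown in Step 7 it cannot carry that meaning.

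The cost is one model term, wider intervals for minutes, and the loss of curvature power in Step 7. The trial may have to report that it cannot locate a threshold in minutes separately from visits.

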[32] we ran several simulations to test the type I error rate for our specific study design of 6 groups, with a binary outcome. We did this for sample sizes ranging from 30 to 40 and assuming an overall baseline improvement rate of either 0.07 or 0.50. We found that the type I error remained below 0.05 for all these situations. Following Fisher’s protected least significant approach, we will first use the omnibus Chi-Square test to test if there is any significant difference between all 6 groups and, if we find one, we will test for pairwise differences between groups. With 34 participants per group, we will have 97% power to find a significant difference between at least two of the 6 groups and 80% power to find a significant difference between Group 6 and Group 2, the treatment groups assumed to differ most in proportion of improvement. Assuming 10% loss to follow-up (as found in our pilot study and in our studies of back pain), we plan to recruit 38 participants in each group, for a total sample size of 228 in the trial.

Our other primary outcome is improvement in the Neck Pain Intensity Score of at least 30% from baseline, which reflects clinically important improvement
[33]. With a final sample size of 34 participants in each group we would have 99% power to find a significant difference between at least two of the 6 groups and 80% power to find a significant difference between Group 6 and Group 2 assuming improvement rates as outlined in Table
4. Therefore, we will have adequate power to assess both our primary outcomes.

It should be noted that both primary outcomes (function and symptoms) will be tested at each time point at the 0.05 level because they address separate scientific questions. Analyses of both outcomes at all follow-up times will be reported, imposing a more stringent requirement than simply reporting a sole significant
[34].

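### A non-significant quadratic term in Model 1.3 cannot show that there is no threshold, and the role of the waitlist group in that model is not stated

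*Protocol article*

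**What the plan says.** In the protocol article, under 'Primary treatment period: primary study outcomes at 5 weeks', the primary analysis is Model 1.1, a logistic regression with one indicator per massage group and the waitlist as reference. The article then concedes that "we have relatively low power to show a significant difference between groups 4, 5, and 6", and that a null result there "could reflect a lack of power or a true absence of additional benefit".

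Model 1.3 is introduced as the response to this. It has a linear and a squared term in total weekly minutes and no adjustment for number of visits. The rule for reading it is: "If the quadratic term is not statistically significant then this would indicate no thresholding effect". The next sentence adds splines as a further look at thresholding.

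The article gives no power for the squared term and no margin for calling a response flat. It does not say whether Group 1 (waitlist) is in Model 1.3. The neighbouring models suggest that it is: Model 1.1 uses it as reference, and Model 1.2 has an intercept plus indicators for 1, 2 and 3 visits per week, which can be estimated only if a zero-visit group is present.

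**The concern.** The section recognises that a non-significant comparison can come from too few participants, and then draws a firm negative conclusion from a different non-significant test on the same participants. A curvature term is usually harder to estimate than a difference between two groups, so the remedy may suffer from the very weakness it is meant to cure.

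The trial looks for the smallest dose that gives the most benefit. A false finding of no threshold suggests that benefit keeps rising up to 180 min per week, and so leans the interpretation towards more massage.

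The unstated role of the waitlist adds a second problem. The planning assumptions contain a large step between no massage and the lowest dose: "we assumed that 7% of the waitlist control group and 35% of Group 2 (60-min weekly treatment) would improve". With the waitlist at 0 min, that step bends the fitted curve whether or not benefit levels off among the doses tested.

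**Working it through.** **Inputs from the article.** 34 evaluable per group; both outcomes "will be tested at each time point at the 0.05 level"; Table 4 NDI rates 0.07, 0.35, 0.40, 0.55, 0.60, 0.70 for Groups 1-6; weekly minutes 60, 60, 120, 90, 180 for Groups 2-6.

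**Assumptions.** Two-sided test, no covariates, waitlist dose 0 when included. The plateau shapes are also assumed: the logit rises in a straight line from 0.35 at 60 min to a top rate at 90 or 120 min and is constant after that.

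**1. Reproduce the stated power.** The article claims "80% power to find a significant difference between Group 6 and Group 2". With i and j responders out of n = 34, the Wald logistic test rejects when |ln(i/(n−i)) − ln(j/(n−j))| / √(1/i + 1/(n−i) + 1/j + 1/(n−j)) > 1.96. Summing exact binomial probabilities over the rejecting tables gives 81.9% for the NDI (0.35 v 0.70) and 80.4% for the second outcome (0.48 v 0.80). The stated figure is reproduced. The sample size also agrees: 34/0.90 = 37.8, rounded up to 38, and 38 × 6 = 228.

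**2. Check the low-power warning.** Under the Table 4 NDI rates, power is 6% for Group 4 v 5, 14% for 5 v 6 and 24% for 4 v 6. The warning is justified.

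**3. Power of the squared term, Groups 2-6 only.** Fit logit(p) = β0 + β1·d + β2·d² with d in units of 60 min, take z = β2/SE(β2), and compute power = Φ(|z| − 1.96) + Φ(−|z| − 1.96). Example, plateau from 120 min at 0.60: β2 = −0.456, SE = 0.361, z = −1.26, power = Φ(−0.70) + Φ(−3.22) = 0.24.

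| Top rate | Plateau from 120 min | Plateau from 90 min |
|---|---|---|
| 0.50 | 12% | 21% |
| 0.55 | 18% | 33% |
| 0.60 | 24% | 47% |
| 0.70 | 41% | 73% |

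Simulations with the likelihood-ratio test agree within a few points, so the working ranges are 11-41% and 20-75%. Taking complements, the rule wrongly declares no threshold in 59-89% and 25-80% of trials.

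Under the Table 4 rates, which rise from 60 to 180 min and contain no defined plateau, the term is significant in about 11-12% (NDI) and 6-7% (bothersomeness column). Those are not missed plateaus and are not counted as such.

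**4. The same term with the waitlist at dose 0 and rate 0.07.**

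| Treated doses | With waitlist | Without |
|---|---|---|
| Logit-linear 0.35 to 0.70, no plateau | about 28-33% | about 5% |
| Flat at 0.35 | about 74% | about 5% |
| Table 4 NDI rates | 62-68% | 11-12% |

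In the first two rows there is no curvature on the logit scale among the tested doses, so the excess over 5% comes entirely from the step between 0 and 60 min. Curvature among the treated doses contributes as well: adding a plateau at a top rate of 0.70 raises significance from about 30% to 64% (from 120 min) or 82% (from 90 min) by the formula in step 3.

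**The case against.** Model 1.3 is a supporting model. Model 1.1 with protected pairwise comparisons is primary, and splines are planned for the same question. The article defines the optimal dose by benefit, adherence and absence of serious adverse events, and no passage makes dose selection depend on the p-value of the squared term. This stands, and it lowers the severity. It does not rescue the sentence: the splines use the same participants, and no decision rule is attached to them.

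It can also be said that power is not uniformly poor. A strong plateau from 90 min would be detected in nearly three quarters of trials. With the waitlist included, simulated plateaus from 90 min at 0.60 and 0.70 are significant in about 90% of trials, so the rule would rarely mislead in that configuration. The first part stands, which is why power is given as a range. The second part is true but gives little comfort: much of that significance reflects the waitlist step, as the no-plateau row shows.

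Finally, the article never says that a significant squared term proves a plateau. A reader might infer that the plan would report one when benefit is still rising, or that the term merely measures the jump from the waitlist. Neither is supported. The first presumes a converse that is not written; the second ignores the contribution from curvature among the treated doses.

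**Conclusion.** The rule is invalid as written and conflicts with the caution given just before it. In the plateau scenarios examined with Groups 2-6 only, it would give the wrong answer in 59-89% of trials when benefit levels off from 120 min and in 25-80% when it levels off from 90 min. These figures rest on 34 per group, a two-sided 0.05 test, no covariates and assumed plateau shapes; the article supplies none, so no single power figure should be quoted.

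The waitlist ambiguity is a separate, lesser defect. With Group 1 at dose 0, the term cannot tell the step from 0 to 60 min from a plateau among the tested doses, and the result can turn on a choice the article does not state. This mainly weakens any reading of a significant term; low power is what defeats the stated reading of a non-significant one.

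A reader might also infer that this test settles the optimal minimal dose. The article does not say so. Severity is moderate.

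**What to change.** - Delete the sentence and state that a non-significant squared term is inconclusive about a threshold.
- Fit Model 1.3 to Groups 2-6 only, or keep Group 1 and give it its own indicator so that the curve is estimated from the treated doses. Say which.
- Report the fitted dose-response curve, from both the quadratic and the planned splines, and the differences between the highest dose and each lower dose, all with confidence intervals. Base any statement for or against a plateau on those intervals.

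The cost is a few lines of analysis wording, with no change to data collection or sample size. The downside is that, with 34 per group, the conclusion about a plateau will often be that the data do not decide it.
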